## Abstract

**Background:**

Alcohol use disorder (AUD) represents a highly prevalent, costly, and often untreated condition in the United States. Post-traumatic stress disorder (PTSD) represents a common comorbidity with AUD which worsens outcomes and decreases functional outcomes. Suvorexant (SUV) shows clear promise as a novel therapeutic candidate to treat AUD and PTSD.

**Methods:**

This study features a promising compound (i.e., suvorexant), the application of a well-established human laboratory paradigm (i.e., alcohol cue reactivity), and a novel early efficacy laboratory model (i.e., practice quit attempt) to provide a cost/time-efficient evaluation of safety and initial efficacy of suvorexant for AUD with comorbid PTSD. Additionally, by collecting both objective and subjective sleep measures, the study provides an assessment of a putative mechanism through which suvorexant jointly addresses an intervening variable common to both AUD and PTSD.

**Discussion:**

The combination of human laboratory modeling and real-world clinical outcomes provides a unique and synergistic set of data that can advance the development of suvorexant and identify its behavioral mechanisms of action. The recruitment of individuals with AUD and PTSD with sleep disturbances and who are intrinsically motivated to quit is a novel approach to screening pharmacotherapies by bridging the gap between experimental studies with non-treatment seekers and clinical trials with treatment-seeking individuals.

**Trial registration:**

ClinicalTrials.gov NCT06679062 “Suvorexant for Treatment of AUD and PTSD (SUV).” Registered on November 12, 2024.

### Introduction

#### Background and rationale {6a}

Alcohol use disorder (AUD) represents a highly prevalent, costly, and often untreated condition in the United States (US). Post-traumatic stress disorder (PTSD) represents a common comorbidity with AUD which worsens outcomes and decreases functional outcomes. Pharmacotherapy offers a promising avenue for treating AUD and PTSD and for improving clinical outcomes for this debilitating comorbidity [1]. While there are FDA-approved medications for AUD and PTSD, these medications are only modestly effective. Therefore, the development and validation of novel treatment targets and compounds is a high-priority research area [2].

Suvorexant (SUV) (Merck & Co., Inc., Rahway, NJ, USA) was the first dual orexin receptor antagonist (DORA) approved for the treatment of insomnia in the US in 2014. A post-marketing trial evaluated the treatment of insomnia with suvorexant in patients with mild to moderate Alzheimer’s disease, and the resulting positive data was included in a label update in 2020. The orexin/hypocretin system is well known for its role in sleep-wake regulation but has more recently been implicated in AUD [3]. Animal models demonstrate that orexin 1 receptor antagonists reduce alcohol drinking in alcohol-dependent mice and alcohol-preferring rats [4–8]. Orexin-2 antagonists also reduce alcohol drinking and reinstatement/relapse in mice and rats [9–11]. Similarly, dual orexin antagonists (DORA) reduce alcohol consumption in alcohol-preferring rats [12, 13]. Given the effectiveness of orexin antagonists in reducing alcohol drinking at the preclinical level of analysis, suvorexant has garnered interest as a drug that can be repurposed to treat AUD [14]. However, these findings have yet to be translated in humans. Understanding if suvorexant can improve drinking outcomes and alleviate PTSD symptoms in a real-world setting is fundamental to the development of SUV as an AUD and PTSD treatment. Moreover, it is critical to elucidate the behavioral mechanisms by which SUV acts.

In addition to the well-established effects in regulating sleep, 15+ years of preclinical data evidence, a key role of the orexin system and DORAs in attenuating (1) drug seeking and self-administration (including alcohol), and (2) PTSD-relevant symptoms including reductions in stress/anxiety [15, 16]. SUV has two key advantages over more traditional somnolent medications (e.g., benzodiazepines) in this population: (1) it uniquely re-regulates polysomnographic (PSG)-measured sleep architecture rather than simply improving onset latency and total sleep time, moving sleep patterns toward homeostasis; and (2) it does not potentiate central nervous system (CNS) depression with alcohol. A phase II clinical trial of SUV for AUD and comorbid insomnia (prevalent in AUD) launched in Australia in 2020 (NCT 03897062) [14]. The National Institute on Drug Abuse (NIDA) medications development branch has placed DORAs/orexin antagonists on its “10 most-wanted” list [17].

Insomnia, addiction, and the orexin system are strongly connected [5]. The orexin system comprises two receptors (ORX-1, ORX-2) and corresponding neuropeptides (ORX-A, ORX-B, respectively) with probable unique functions related to sleep (ORX-2), stress/anxiety modulation (ORX-1), and energy homeostasis [6, 7]. Note that each of these areas is highly problematic in PTSD, with sleep problems being the most cited comorbid complaint in veterans with PTSD [8] followed by stress/anxiety symptoms. Similarly, disruption of sleep and heightened stress-induced cue reactivity are also highly prominent in AUD, driving motivation for ongoing use and relapse after abstinence [9, 10]. DORAs, including the proposed Food and Drug Administration-approved medication suvorexant, modulate both ORX-1 and ORX-2, serving as a biologically ideal target for addressing the overlapping symptoms in AUD and PTSD. Specifically, DORAs can effectively regulate sleep and restore normal sleep architecture [15] and attenuate PTSD symptoms [16] and motivation to use alcohol in preclinical models. The University of Texas Health Science Center at Houston (UTHealth) group published the first human study of orexin antagonism in substance use disorder (cocaine) with demonstrated effects on sleep and HPA-axis reactivity [18].

SUV shows clear promise as a novel therapeutic candidate to treat AUD and PTSD. Animal studies have shown that orexin receptor antagonists reduce both alcohol administration and relapse-like behavior in alcohol-dependent mice and alcohol-preferring rats [4–13]. However, to date, no published studies have translated these findings to clinical AUD samples or AUD + PTSD comorbidity. Understanding if suvorexant can improve drinking outcomes and alleviate PTSD symptoms in a real-world setting is fundamental to the development of this dual orexin receptor antagonist as an AUD + PTSD treatment. Moreover, elucidating the behavioral mechanisms by which suvorexant acts is also critical. Specifically, animal research has shown multiple potential mechanisms underlying suvorexant efficacy including reducing craving, reducing motivation, and relieving withdrawal symptoms. The protocol team has intentionally set a “wide net” of potential mechanisms given the scarce literature on the effects of suvorexant in AUD. Consideration of sleep, craving, and mood as behavioral mechanisms is consistent with work by Mason et al. [19–21] in medication development.

This study features a promising compound (i.e., SUV), the application of a well-established human laboratory paradigm (i.e., alcohol cue reactivity), and a novel early efficacy laboratory model (i.e., practice quit attempt) to provide a cost/time-efficient evaluation of safety and initial efficacy of suvorexant for AUD with comorbid PTSD. Additionally, by collecting both objective and subjective sleep measures, the study provides an assessment of a putative mechanism through which suvorexant jointly addresses an intervening variable common to both AUD and PTSD. The combination of human laboratory modeling and real-world clinical outcomes provides a unique and synergistic set of data that can advance the development of suvorexant and identify its behavioral mechanisms of action. The recruitment of individuals with AUD + PTSD with sleep disturbances and who are intrinsically motivated to quit is a novel approach to screening pharmacotherapies by bridging the gap between experimental studies with non-treatment seekers and clinical trials with treatment-seeking individuals. This is relevant given the wide range of differences between treatment seekers and non-treatment seekers with AUD [22, 23]. The study will also rely on an in vivo cue-reactivity paradigm which is highly consistent with the Human Laboratory Program approach by the National Institute on Alcohol Abuse and Alcoholism, a gold standard in medication screening. Assessments of PTSD symptomatology and sleep provide a comprehensive picture of clinical mechanisms of action for this patient population. Lastly, the novel practice quit paradigm has high ecological validity and the potential to detect clinically meaningful effects. Together, these design features enhance the study innovation and its overall scientific impact.

The successful completion of this study will set the stage for a larger phase II clinical trial of suvorexant for AUD and comorbid PTSD. Given the high prevalence of AUD + PTSD and the high acceptability of SUV as a therapeutic agent, the study has the potential to be transformative in the treatment of AUD + PTSD and in uncovering the therapeutic benefits of SUV.

### Objectives {7}

The primary objective of this study is to assess the initial efficacy of SUV (20 mg) in improving sleep metrics.

The secondary objectives of this study are:To assess the effect of SUV (20 mg) on cue-induced alcohol craving.To evaluate the effect of SUV (20 mg) on the mean number of drinks per drinking day.To evaluate the effect of SUV (20 mg) on drinks per day during the medication period over a 14-day quit attempt.To assess the initial efficacy of SUV (20 mg) in reducing PTSD symptoms.

The exploratory objectives of this study are:To assess the efficacy of SUV (20 mg) in improving sleep latency onset (SLO), wake after sleep onset (WASO), and total sleep duration via actigraph data.To evaluate the effect of SUV (20 mg) on National Institutes of Health Patient-Reported Outcomes Measurement Information System (PROMIS) sleep scale scores.

### Trial design {8}

This is a randomized, double-masked, placebo-controlled study to evaluate preliminary efficacy and safety of SUV (20 mg) for sleep disturbance in AUD and co-occurring PTSD symptoms in approximately 76 randomized men and women veterans and non-veterans between the ages 21 and 65. Following a 7-day placebo run-in, participants will be randomly assigned to receive SUV (10 mg (days 0–6) and 20 mg (days 7–13)) or matched placebo. Participants will be stratified on site, sex, and level of sleep disturbance (Insomnia Severity Index (ISI) score). Post-randomization, all participants will complete an alcohol cue-reactivity paradigm prior to the initial dose of study medication. The alcohol cue-reactivity paradigm is an established laboratory assessment of craving during which participants are exposed to real alcohol and water cues in a bar laboratory setting. Participants will then take their first dose of medication. Participants will begin the real-world practice quit attempt, during which they will attempt to stop drinking for 2 weeks. Participants will complete daily virtual diaries and visits to assess sleep, past-day drinking, and alcohol craving. Participants will return to one of the clinical sites on study day 14 to complete an alcohol cue-reactivity session, to assess post-medication craving. PTSD symptoms will be assessed via Clinician-Administered PTSD Scale for Diagnostic and Statistical Manual of Mental Disorders, Fifth Edition (DSM-5) (CAPS-5) and PTSD Checklist for DSM-5 (PCL-5) at baseline, at day 7, and at day 14 of treatment with SUV or matched placebo.

## Methods: participants, interventions, and outcomes

### Study setting {9}

This study will utilize 2 sites; one in Houston, TX (UTHealth) and one in Los Angeles, CA (UCLA). The UTHealth’s primary recruitment center for veteran and non-veteran population will be the UTHealth Trauma and Recovery Center (TRC). UCLA Department of Psychology will be the primary research site in California and will collaborate with the West Los Angeles VA Medical Center to recruit the veteran population.

### Eligibility criteria {10}

To be enrolled in this study, participants *must meet* the following criteria.Age between 21 and 65.Meet current (i.e., past 12 months at day −7/−6) DSM-5 diagnostic criteria for moderate or severe AUD as determined by the MINI.Currently experiencing PTSD symptoms at screening (day −7/−6) as indicated by PCL-5 cut-score > 30.Intrinsic motivation to reduce or quit drinking (defined as self-reported intention at screening to reduce or quit drinking within the next 6 months) and to receive PTSD treatment.Must have an ISI score equal to or >7 (subthreshold insomnia). ISI score below 7 at screening will not be included or proceed beyond the screening day.Agree to abstain from all other sleep medications (starting at day −7).Have a place to live in the 2 weeks prior to randomization (day 0) and not be at risk that s/he will lose his/her housing in the next month.

To be enrolled in this study, participants *must not meet* the following criteria.A current (past 12 months at day −7/−6) DSM-5 diagnosis via the Mini-International Neuropsychiatric Interview (MINI) of substance use disorder for any substances other than alcohol, nicotine, or marijuana (< moderate level on DSM-5).A lifetime DSM-5 diagnosis via the MINI of schizophrenia, bipolar disorder, or psychotic disorder.Positive urine test for any recreational drugs other than marijuana at screening (day −7/−6).Current clinically significant alcohol withdrawal (i.e., score ≥ 10 on the Clinical Institute Withdrawal Assessment Alcohol Scale Revised (CIWA-Ar)).Currently pregnant, nursing, or no reliable method of birth control (females only).Any clinically significant medical condition that would preclude safe participation in the study (e.g., narcolepsy, seizure disorder, or other clinically significant cardiovascular, hematologic, hepatic, renal, neurological, or endocrine disorders).Use of suvorexant (within 30 days of day −7).Currently on prescription medication that contraindicates use of suvorexant (including moderate or strong cytochrome P450 3 A modulators (CYP3A inhibitors and inducers)).Hepatic insufficiency (AST/ALT > 5× upper limit of normal (ULN)).Suicidal ideation determined by ≥ moderate Columbia Suicide Severity Rating Scale.Inability to provide evidence of 48-h alcohol abstinence (self-report, breath alcohol (BrAC), ethylglucuronide (EtG) testing) at day 0 and failure after second attempt at 48-h abstinence (see Fig. 1).

**Fig. 1 Fig1:**
[figure not shown]
The study design is a double-blind, randomized, phase II study comparing the effectiveness of 20 mg oral suvorexant (SUV) versus placebo (PLC) (1:1), with a 1-week placebo run-in phase for all participants

### Who will take informed consent? {26a}

Potential participants are given ample time to consider the informed consent. They may have as much time as needed (no time limit) to read and consider the risks and benefits of the study participation, and they may involve family members, significant others, and the primary treatment team in the decision on whether or not to participate in the study.

Prior to entering the study, a member of the study team provides the potential participant with detailed information regarding the study’s purpose, procedures, potential risks and benefits, alternative treatment, compensation, and other required elements. This is done by a study team member in a private setting and documented on a signed and dated informed consent form. The investigators are responsible for answering questions pertaining to the study medication and their side effects. A participant’s willingness to take part in the study is subsequently documented in the medical records. If a participant agrees to participate, his/her consent is recorded on the Institutional Review Board (IRB)-approved informed consent form. Informed consent requires that the participant understands the details of the study, including its risks and benefits, and agrees without coercion to participation. The signed and dated consent form is distributed to participant’s study file (original), research pharmacy files (copy—if randomized), and participant (copy). A note is entered by the study staff into the participant’s medical record to document the process of informed consent.

All participants must have the capacity to provide their own informed consent. Surrogate consent is not allowed. Only those patients with capacity for informed consent are eligible. Persons who lack capacity to give independent informed consent (i.e., severe cognitive disorder such as dementia, severe traumatic brain injury, or other known cognitive or psychotic disorder that impairs decision-making) are not eligible to be enrolled. Persons with a terminal illness, minors, and prisoners should not be recruited or enrolled in this study.

Protection of participants from harm must be balanced against the potential for benefit to participants themselves, and to other persons with their disorders, that may arise from research participation. Since new treatments must eventually be tested in persons suffering from the condition, a policy totally excluding vulnerable participants from research would preclude the development of improved treatment for persons with AUD or PTSD. This study specifically recruits veterans, service members, first responders, and community volunteers with AUD or PTSD, which may be considered a vulnerable patient population. Vulnerable populations, i.e., prisoners, individuals with mental retardation, minors, persons with dementia or severe cognitive disorders, and persons deemed legally incompetent, are not eligible for this study. The decision-making capacity of individuals with AUD or PTSD at this stage of recovery is typically intact; however, veterans specifically are accustomed to taking and following direct orders, which requires a greater need for the researcher to prevent coercion, either directly or indirectly. Potential participants are given ample time to read and consider the informed consent, with other treatment options explained in the consent form. Family members, significant others, and primary treatment teams may also be involved in the decision-making process if the participant wishes. Veterans specifically are also informed that declining participation in a study does not change their eligibility for VA services, treatment, disability, or other VA benefits. Those individuals who are economically or educationally disadvantaged may be considered vulnerable. The VA population includes individuals in this category; however, the study keeps payments to participants at a minimum to avoid coercion based on economic hardship. In addition, the informed consent is written at a grade school level of education to minimize vulnerability to the educationally disadvantaged.

### Additional consent provisions for collection and use of participant data and biological specimens {26b}

Participant data and biological specimens used to evaluate eligibility and study compliance (i.e., urine sample, ECG, CBC, CMP) will be disposed of after testing.

## Interventions

### Explanation for the choice of comparators {6b}

The trial is placebo-controlled due to there being no universal standard-of-care medication for AUD or PTSD treatment.

### Intervention description {11a}

The study will utilize 10 mg and 20 mg SUV tablets and matching placebo obtained from Merck & Co., Inc., Rahway, NJ, USA. One SUV tablet (10 mg/20 mg) or placebo tablet will be taken orally once daily 30 min before bed with at least 7 h remaining prior to planned awakening. Each participant will be given a placebo run-in (day −7 to day −1). On day −2, participants will be prompted to initiate a 48-h abstinence period. If the study team determines appropriate quit attempts were successful on (verified by self-report + BrAC + EtG) baseline (day 0), the participant will be randomized to SUV or placebo and administered 10 mg SUV or placebo capsules for an additional 7 days (day 0 to day 6). On day 7, the participant previously randomized to SUV will be given 20 mg SUV, and the participant previously randomized to placebo will continue with placebo. The participant will be administered the remaining number of capsules (days 7–13).

### Criteria for discontinuing or modifying allocated interventions {11b}

Participants are free to discontinue study treatment or withdraw from participation in the study at any time, or the investigator may terminate a participant’s participation; however, these are two different actions that result in different study follow-up paths.

The investigator may discontinue study treatment for a participant or withdraw participation in the study if:Any clinical adverse event (AE), laboratory abnormality, or other medical condition or situation occurs such that continued receipt of study treatment or participation in the study would not be in the best interest of the participant.The participant meets an exclusion criterion (either newly developed or not previously recognized) that precludes further study participation.The participant demonstrates an inability to comply with the verbal and written study instructions and/or procedures or exhibits difficult behaviors (e.g., abusive, violent, aggressive).The investigator decides that continuing in the study would be harmful to the participant.The participant uses illegal drugs while in the study.The participant needs to take medications that are not allowed while in this study.The participant is unable to keep appointments or complete study procedures as instructed.The participant has a bad reaction to the study drug such that s/he can no longer continue to take them.The study is canceled by PASA/DOD (project sponsor), Merck & Co., Inc., Rahway, NJ, USA (MISP grantor), the responsible IRB(s), or via recommendation of the DSMB.The patient is suspected of abusing the medication by taking larger doses than prescribed.

### Strategies to improve adherence to interventions {11c}

Potential participants will be educated on study procedures during the consent process and screening visit to help with adherence and understanding of the study. Various study retention techniques will be used throughout the study such as reminder calls and reimbursement for study visits to keep participants engaged in the study.

The study will also implement nightly text-based medicine prompts and verification through the Cell-phone Assisted Remote Observation of Medication Adherence (CAROMA) check-in. Video will capture the patient self-administering the capsule, increasing verification of compliance at high rates [24].

### Relevant concomitant care permitted or prohibited during the trial {11d}

Concomitant medications will be reviewed and documented by the study physician(s) at screening and all follow-up visits. Potential concomitant medications to be aware of include co-administration of CNS depressants and drugs that increase blood levels.

Per study exclusionary criteria, participants may not be taking the following medications: moderate CYP3A inhibitors, strong CYP3A inhibitors, strong CYP3A inducers, digoxin, and narcolepsy medications.

### Provisions for post-trial care {30}

Post-trial care may continue after study participation if any adverse events remain. The study physician will contact the participant via phone to follow up and close out any adverse events. Participants who drop out of the trial due to adverse events do not fall into this category.

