### Sample size {14}

Sample size for this study was determined based on the prior published studies of suvorexant effect on ISI which suggest that the standard deviation (SD) is between 6 and 8 points for the change from baseline. Based on a two-sided *t*-test of treatment effect with 80% power and alpha set at 0.05, the study would be able to detect a medium effect size (about 0.66, e.g., mean difference of 5.5 with SD of 7) with a total of 76 participants. This total number of participants includes those that complete screening, placebo lead-in, and at least day 0 study activities through randomization (and assuming no more than 7% attrition/loss to follow-up).

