#### Medical procedures and/or assessments

Breathalyzer: Breathalyzer tests are used to measure participants’ breath alcohol concentration (BrAC). Samples >0.01 g/dl are considered positive. Results are kept in research records and not entered in medical records.Ethylglucuronide (EtG) testing: Ethylglucuronide is a byproduct of ethanol (alcohol that one drinks) and glucuronide, a common biological compound made in the liver that binds various toxins and drugs in the body that allows them to be excreted in the urine. When someone drinks even relatively small amounts of alcohol, EtG is formed and can be detected in the urine.Demographics: The interviewer asks the respondent for his/her date of birth, race, if he or she considers himself or herself to be Hispanic or Latino, and highest-grade level or degree received at the time of the interview.Medical history: This measure is a broad screening tool to collect information on a participants’ medical history, including recent hospitalizations, and check for conditions such as diabetes, liver disease, and kidney disease. It is comprised questions to cover the following areas: allergies, asthma, head, ears, eyes, nose, throat (HEENT), cardiovascular, renal, hepatic, pulmonary, gastrointestinal, musculoskeletal, neurologic, psychiatric, dermatologic, metabolic, hematologic, endocrine, genitourinary, reproductive system, seizure, infectious disease, inflammatory or auto-immune disorders, and diabetes. Screening will include questions to ensure patients are not currently taking any CPY3a inhibitors.Physical examination (PE): A targeted PE will include assessments of the head, eyes, ears, nose, throat, skin, thyroid, neurological system, lungs, cardiovascular system, abdomen (liver and spleen), lymph nodes, and extremities. Height and weight measurements will be taken during screening.Electrocardiogram (ECG): 12-lead ECGs will be obtained using a machine that automatically calculates heart rate and determines intervals for PR, QRS, QT/QTc, and PRT axes.Colombia Suicide Severity Rating Scale (C-SSRS): is a short questionnaire that screens for individuals at risk for suicide.Adverse events: All AEs occurring during the clinical trial will be collected, documented, and reported by the principal investigator/designated study staff according to the specific procedures detailed in section 22 below. Additionally, study staff will assess patients for any medical or psychiatric side effects by asking the participant “How have you been feeling since I saw you last?” and in a manner consistent with Systematic Assessment for Treatment of Emergent Events (SAFTEE) guidelines [25]. Study staff will also review the previous Adverse Event Form and inquire whether any of those events are continuing. Each new or unresolved adverse event will be recorded on the Adverse Event Case Report Form using a brief verbatim term, a severity ranking, and any additional description, according to the procedures. If an adverse event is reported that requires medical attention, it will be reported to a study clinician immediately for review. The PI/trained staff member will review each AE to assess their possible relationship to study medications and expectedness.Prior/concomitant medications (con-meds): Concomitant medications (con-meds) are other prescription medications, over the counter (OTC) drugs, or dietary supplements that a study participant takes in addition to the drug under investigation. Participants are asked to bring all their current medications with them at the time of their screening appointment.Actigraph: This wearable device will be used to measure the SLO and WASO variables in detecting activity and sleep patterns of participants. Participants will be given this device upon successful screening into the study.

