### Adverse event reporting and harms {22}

All AEs will be recorded on the study CRFs and entered into REDCap. Timely mandatory reporting is required for AEs that are serious, unexpected, and definitely, probably, or possibly related to the study drug. For all other events, the site will follow institutional policy for reporting to the IRB. Reporting to the DSMB will occur via study reviews occurring on a prescheduled frequency.

Each AE will be classified by the PI as serious or non-serious. Serious AEs (SAEs) will be reported by the site to their local IRB and to PASA within 24 h of identification. Initial reports will include as much information as possible but, at a minimum, should include the event term, onset date, severity, serious criterion, relationship to study drug, date of resolution (or continuing, if known), action taken with study drug because of the reported event, and an event outcome (if known). Initial reporting will be followed within 2 days by reporting missing AE characteristics and a description of the event.

Determination of whether the event may be unexpected and at least possibly related to the study drug will be made by the study clinical team in collaboration with PASA medical monitor. Any SAEs that are deemed related and unexpected will be submitted by PASA Leadership in conjunction with the study team in a safety report to the FDA, drug manufacturer, DSMB, and participating investigators. Clinical sites will follow local IRB guidelines for submission of any unexpected and related SAEs that occur. Participating investigators and DSMB will be notified by PASA Leadership in conjunction with the study team as soon as possible, but no later than 15 calendar days after it is determined the SAE qualifies for reporting. Furthermore, participating investigators and DSMB will be notified of any unexpected fatal or life-threatening suspected adverse reaction as soon as possible, but no later than 7 calendar days after initial receipt of the information.

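### As worded, the post-trial care text excludes participants who drop out because of an adverse event from the only close-out call described for open adverse events

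*Protocol article*

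**What the plan says.** The section Provisions for post-trial care {30} of the protocol article has three sentences. The first allows care to go on after participation when adverse events are unresolved. The second says what that care is: "The study physician will contact the participant via phone to follow up and close out any adverse events". The third limits who receives it: "Participants who drop out of the trial due to adverse events do not fall into this category".

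The group named in the third sentence is foreseen elsewhere. Criteria for discontinuing or modifying allocated interventions {11b} lists, among the grounds on which the investigator may stop treatment or withdraw a participant: "Any clinical adverse event (AE), laboratory abnormality, or other medical condition or situation occurs such that continued receipt of study treatment or participation". A bad reaction to the study drug is listed as a further ground. The same section says of stopping treatment and leaving the study that "these are two different actions that result in different study follow-up paths". It does not say what either path contains.

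**The concern.** The only category that section {30} sets up is people with unresolved adverse events whom the study physician will phone. The third sentence takes out of it those who left because of such an event. This reverses the usual order of priority: an event severe enough to end participation is the one whose outcome most needs to be known, both for the participant and for the tolerability record.

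Safety is part of the trial's stated purpose. Trial design {8} describes the study as one "to evaluate preliminary efficacy and safety of SUV (20 mg" dose. What is at stake is modest: the final outcome of a treatment-limiting event still open at exit, and one safety contact with that person.

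The concern covers only participants who leave the trial. Someone who stops the drug but stays in the study is not excluded by this sentence.

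**Working it through.** The main check is a reading of the text: does any other section give a participant who has left because of an adverse event a contact equivalent to the call in {30}?

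| Section of the protocol article | What it provides | Does it reach someone who has left because of an adverse event? |
|---|---|---|
| Provisions for post-trial care {30} | Physician phone call to close out open events | No; the third sentence excludes them |
| Criteria for discontinuing {11b} | States that follow-up paths differ | Unknown; the paths are not described |
| Participant timeline {13}, virtual follow-up on days 1–6 and 8–13 | Safety self-report at daily visits | No; it is tied to visits that a leaver no longer attends |
| Participant timeline {13}, in-person visits on days 7 and 14 | Scheduled visits of participants still in the study | No contact after exit is described |
| Medical procedures and/or assessments, under {18a} | Staff ask whether earlier events continue. Also: "If an adverse event is reported that requires medical attention, it will be reported to a study clinician immediately for review" | No contact after exit is stated |
| Adverse event reporting and harms {22} | All events recorded; serious events reported within 24 h. Also: "Initial reporting will be followed within 2 days by reporting missing AE characteristics and a description of the event" | Completes the report of a serious event; does not follow the event to resolution. Nothing equivalent for non-serious events |

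In {22}, the resolution date and outcome of a serious event are to be supplied if known, so a report can be complete while the event is still open. Section {30} is therefore the only place that describes closing out an open event after participation, and it names the group it leaves out.

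**How many participants.** The article states no figure for this, so there is nothing to reproduce. A bound follows from Sample size {14}, which gives 76 participants, "assuming no more than 7% attrition/loss to follow-up".

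- Leavers for all reasons at the planned limit: 0.07 × 76 = 5.32, about 5.
- The share who leave because of an adverse event is not stated. Assume a share *s*, and that every such event is still open at exit. Number affected = *s* × 5.32.
  - *s* = 20%: 0.20 × 5.32 = 1.06, about 1
  - *s* = 50%: 0.50 × 5.32 = 2.66, about 3
  - *s* = 100%: 1.00 × 5.32 = 5.32, about 5

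For each of these participants, the sentence removes the close-out follow-up by phone and nothing else.

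**The case against.** The strongest reply is that the third sentence sorts people and does not abandon them. The section is about care after the trial. Participants who leave early for an adverse event may simply belong to a different procedure, and {11b} says that different follow-up paths exist. The content of those paths is operational detail that an article normally leaves to the full protocol, which {31c} says will be released. On this view the sentence is at most unclear.

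Much of this is fair. The softer reading cannot be ruled out, and the text does not prove that these participants would go without follow-up in practice. The undescribed paths in {11b} are not held against the article here. However, the sentence in {30} is not a silence to be filled by another document. It is a stated exclusion that points to no other procedure, and a site following it literally would not make the call.

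Three further points can be made:

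- **Other safeguards.** An event that leads to dropout will usually have been recorded and graded already, and serious events have their own reporting route. This is right, and it confines the loss to the final outcome of events still open at exit.
- **The counts.** The 7% is an all-cause planning limit, not a rate of dropout for adverse events, and the shares are assumed. This also stands. The figure of 5 is the upper end at that limit, and the actual number could be zero or one.
- **The remedy.** Following events until resolved or stable is more than one call per person. This is true for an event that runs on, but section {30} does not limit completers to a single call either.

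**Conclusion.** The point holds as a statement about the wording. Section {30} excludes participants who drop out because of an adverse event from the only close-out contact the article describes, and no other section supplies one. Whether they would in fact be missed depends on follow-up paths that the article mentions but does not describe.

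The size is small: at most about 5 of 76 participants at the planned attrition limit, and about 1 to 3 if 20% to 50% of leavers go because of an adverse event that is still open. These counts rest on the planned limit being reached and on the assumed shares. If attrition exceeds 7%, they rise in proportion.

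Occurrence, severity and relatedness of the events are still recorded. Sample size, power, the significance level and the efficacy analyses are unaffected. This is an inexpensive improvement to safety follow-up that should be made, and no threat to the trial's conclusions.

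**What to change.** Replace the third sentence of Provisions for post-trial care {30} with wording such as:

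> Any adverse event still open when a randomized participant leaves the trial for any reason, including an adverse event, is followed by the study physician by phone until resolved or stable, subject to the participant's consent.

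If the full protocol already has a follow-up path for these participants, it is enough to delete the exclusion and cite that path.

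The cost is one sentence, plus phone follow-up of a kind already planned for other participants, for about 5 people at most at the planned attrition limit. An event that takes long to settle may need more than one call. No assessment, visit or analysis changes.
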